## Abstract

**Introduction:**

Besides functional outcomes, mental health and health-related quality of life (HRQoL) are significant measures in chronic diseases, such as stroke. Post-stroke depression (PSD) is an important complication affecting up to one in three stroke survivors. So far, specific programs to screen, detect and treat these patients are lacking but might be a crucial component in stroke aftercare.

**Methods:**

Between March 2024 and Febuary 2025 all consecutive adult patients with stroke, admitted to the University Hospital of Augsburg, are screened for signs of depression (PHQ-9 (Patient Health Questionnaire-9) score of ≥ 10). Eight weeks later, those patients with persisting signs of depression will be randomized to receive either a behavioural activation intervention or a mindfulness-based intervention via telephone. Depressive symptoms will be assessed at baseline (V1), after 84, 180 (V2-V3) and after 365 days (V4) using the PHQ-9 score. Secondary outcomes include the functional outcome, quality of life (EuroQol-5 Dimensions; EQ-5D), overall functioning, and incidence of major cardiovascular events including recurrent transient ischemic attack, stroke, and mortality.

**Perspective:**

Our aim is to provide proof-of-concept evidence for the efficacy of telepsychological need-adapted interventions for patients with post-stroke depression. Regular screening for PSD with implementation of a feasible treatment option could reduce the long-term prevalence of PSD and improve quality of life.

**Trial registration:**

This trial was registered at German Clinical Trials Register (DRKS) on 07.03.2024, ID: DRKS00033792. German Clinical Trials Register (drks.de).

## Introduction

Globally there were 12.2 million incident and 101 million prevalent cases of stroke in 2019. Thereby, stroke caused 143 million disability-adjusted life-years (DALYs) [1]. Assessing the functional status and disability after stroke is important, but stroke severity measures, such as the National Institutes of Health Stroke Scale (NIHSS), do not capture other important aspects well, such as health-related quality of life (HRQoL) [2]. Major limitations of HRQoL after stroke are neuropsychological disorders, especially post-stroke depression (PSD). Although often being overlooked [3] PSD is already one of the most common neuropsychological complications after stroke, affecting up to 31% of stroke survivors [4] and may also have an increasing incidence and prevalence in the future. Hence, effective, and resource-efficient treatment options are needed.

PSD has a complex impact. It is associated with a poorer recovery of activities of daily living (ADL) [5]. It also affects, among other factors such as stroke severity, ethnicity and socioeconomic status, the return to work rate, which ranged from 28 to 88% among stroke patients [6]. At the same time, the prevalence of depression and anxiety is higher in patients who do not return to work [7]. Therefore, PSD is not just a factor that reduces HRQoL, but is also a health- and socio-economic issue that is associated with higher impairment of ADL, less successful rehabilitation, and lower return to work rates.

Current treatment options include pharmacotherapy, psychotherapy, electroconvulsive therapy, hyperbaric oxygen therapy and neuromodulation [3]. Pharmacotherapy is part of standard treatments, also being recommended in guidelines [8], but there is not only conflicting evidence about specific drug class superiority [8] but also contradictory evidence about its effectiveness in general [3]. Besides this rather weak evidence, it is known that antidepressants may have severe adverse outcomes, such as increased mortality in stroke survivors with depression, gastrointestinal bleeding, falls and factures [9]. Such risks are not present in psychological therapy of PSD. Nevertheless, a recent Cochrane review found, that there is very low certainty of evidence, that psychological therapy may reduce the incidence of PSD at the end of treatment. This was mainly attributed to the methodology of the respective trials [10]. The treatment methods ranged from problem-solving therapy, cognitive behavioural coping therapy [11] to a “solution-focused brief therapy” [12] and a “motivational interviewing” [13]. Participants were treated for four weeks up to 52 weeks [10]. Another study examined repeated psychosocial-behavioural interventions with drug treatment versus drug treatment only [14]. Less patients met the study criteria for depression at the end of each treatment [10, 14]. These treatments were carried out in a direct person-professional interaction, thus limiting the accessibility. Telepsychological interventions, delivered remotely, can overcome this barrier, thus being resource-efficient treatment options, eliminating the need for patients with disability after stroke or therapists to travel. Furthermore, they improve scalability in times of growing demands. Telepsychological interventions have been studied in general and video conferenced mental and behavioural health services already showed promising results in patients with depression [15].

To overcome the downsides of pharmacotherapy and of conventional psychotherapy, we examine the short- and long-term efficacy of telepsychological Behavioural Activation (BA) therapy for patients with PSD in this monocentric randomized and controlled rater-blinded study. BA represents an innovative and evidence-based advancement of classical behaviour activation. It integrates techniques from Acceptance and Commitment Therapy (especially value work) and Dialectical Behavioural Therapy (particularly validation techniques and emotion regulation strategies) in a highly structured and easily learnable manner. Stemming from the reinforcement loss model of depression, its core focus lies in planning, implementing, and rebuilding value-oriented behaviour, enabling patients to gain long-term, stable access to positive reinforcement. The control group will receive guided mindfulness-based practices [16].

Identification of patients with PSD is a crucial part of PSD management, because it is frequently overlooked even though its high prevalence. Screening for PSD helps to avoid neglecting patients who require care, but also conserves resources by not having to treat every patient with stroke preventively, as it has been suggested in previous studies.

We hypothesize that telepsychological interventions are feasible and effective treatment options for PSD, thus contributing to rehabilitation outcomes and overall improvement of HRQoL after stroke.

## Methods

### Aim of the trial

The presented interventional study is part of the digiBRAVE (digitale Bayerische (Früh-)-Diagnostik-, Prävention und Therapieprogramm Depression) program, and will be carried out at the University Hospital of Augsburg and remotely. DISCOVER is designed as a proof-of-concept study, since this is the first concept of using Behavioural Activation (BA) therapy vs. a control group to treat depressive symptoms in patients with stroke.

The Department of Neurology at the University Hospital Augsburg is a tertiary stroke center and the sole hospital providing acute stroke care for all stroke patients in the city of Augsburg and the surrounding county (around 750,000 people in total), which helps to minimize selection bias. Approximately 1,800 patients with acute stroke are treated each year at the University Hospital of Augsburg.

### Study description and study design

We compare the efficacy of telepsychological Behavioural Activation (BA) therapy with guided mindfulness-based practices for patients with PSD in this monocentric, randomized, controlled, rater-blinded trial. The allocation ratio is 1:1. Repeated follow-ups are planned up to one year after enrolment to assess short- and long-term effects.

Baseline characteristics such as age, sex, cerebrovascular risk factors, history of relevant diseases, history of preceding strokes, stroke etiology, stroke severity (NIHSS and modified Rankin scale (mRS)) at admission and discharge and acute stroke treatment will be gathered from the patients’ chart.

Following the screening visit (V0), patients with persisting depressive symptoms after eight weeks (56 days) at the baseline visit (V1) are randomized either to the intervention or the control condition and are invited to three more visits until the end of study visit (V4, day 365). The primary outcome is evaluated at visit 2 (day 84), the secondary outcomes at the end-of study visit (V4). Table 1 shows the detailed scope and the frequency of study visits.

**Table 1 Tab1:**
[figure not shown]
Schedule of enrolment, interventions, and assessments

We use an external randomization performed by a party not involved in the recruitment and treatment of patients. Patient selection will follow a systematic strategy and is documented according to CONSORT. The randomization list will be produced by a statistician not involved in the study.

For the primary outcome (of depressive symptoms between baseline and day 84) assuming repeated measures ANOVA as analysis method, a type I error probability of α = 0.05, a power of 1- β = 0.8, two groups at V2 (day 84), and a correlation between the measurements of *r* = 0.5, medium effects of f = 0.30 or higher can be detected for the within-subject factor time, for the between-subject factor group, and for interactions between time and group with a total necessary sample size of 68 (34 participants per group) at V2. No previous data is available to estimate the expected effect size. These calculations were performed with G*Power 3.1.9.7 [17].

The intention-to-treat (ITT) population includes all patients as randomized, and the modified intention-to-treat (mITT) population includes all patients as randomized + having received the first visit after signed informed consent (baseline visite). The safety population includes all patients as randomized. Assuming a drop-out rate of 10% during the intervention period, 76 patients are planned to be randomized. The per protocol (PP) population will include all participants without major protocol violations. All primary analyses will be performed on the ITT population. For the primary endpoint, a linear mixed model will be performed and in cases of significant ‘group x time’ interactions, post-hoc comparisons corrected for multiple testing will be performed. Continuous secondary endpoints will be analysed using linear mixed models and subsequent post-hoc tests if the requirements for this strategy are met (tested by Kolmogorov-Smirnov tests and Levene’s tests). In cases where the assumptions of normality or variance homogeneity are violated, a monotonic transformation of variables will be performed. If this first step is not successful, corresponding non-parametric tests will be used. Side-effects, adverse events (AE) and severe adverse events (SAE) will be analysed with descriptive statistics and likelihood-ratio tests. Demographic information will be shown for each group separately, and they will be compared between the groups. Dichotomous variables will be analysed with likelihood-ratio tests and continuous variables will be analysed using analyses of variance or respective non-parametric tests. Baseline characteristics are presented as mean (M) ± standard deviation (SD) for normal distributed and additionally median and 25th and 75th quartiles (Q25, Q75) for all continuous variables. Categorical variables are given as numbers (n) and percentages (%). An interim analysis is not planned. The statistician will be blinded for the groups during the phase of data-analyses. Prior to the start of the trial, a statistical analysis plan will be developed.

All analyses will be performed at a significance level of α = 0.05.

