### Outcome measures

#### Primary outcomes

Change in Patient Health Questionnaire-9 (PHQ-9) score from Baseline (V1) to day 84 (V2).

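### The single day-84 primary endpoint is tested through a group-by-time gate and corrected post-hoc comparisons; one baseline-adjusted day-84 contrast would be clearer and usually more powerful

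*Protocol article*

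**What the plan says.** All places are in the protocol article.

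- **Endpoint.** Primary outcomes lists one item, the change in PHQ-9 from V1 to day 84. Study description and study design says that it is evaluated at visit 2. PHQ-9 change to days 180 and 365 appears under Secondary outcomes.
- **Analysis.** The statistical text in Study description and study design uses a linear mixed model for the primary endpoint. Where the group-by-time interaction is significant, "post-hoc comparisons corrected for multiple testing will be performed". The text does not say which visits enter the model, whether V1 is a response or a covariate, how many post-hoc comparisons there are, or which result makes the trial positive.
- **Sample size.** The calculation was made "assuming repeated measures ANOVA as analysis method", for symptoms between baseline and day 84, with "a type I error probability of α = 0.05, a power of 1- β = 0.8" and "a correlation between the measurements of *r* = 0.5". It claims that "medium effects of f = 0.30 or higher can be detected for the within-subject factor time", and equally for group and for the interaction, with 68 patients (34 per group) at V2. It adds: "No previous data is available to estimate the expected effect size".
- **SAP.** A separate SAP is announced. It was not available for this review.

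**The concern.** The trial asks one confirmatory question: does PHQ-9 at day 84 differ between behavioural activation (BA) and mindfulness? A gate followed by corrected comparisons suits several visits or several arms of equal standing. Here it has two drawbacks.

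1. **No single decisive test.** A reader cannot tell whether the trial is positive when the interaction is significant or only when a corrected day-84 comparison is significant as well.
2. **Efficiency.** Repeated measures ANOVA with baseline as a response does not use the fact that randomization makes the expected baseline means equal. An analysis that adjusts for V1 PHQ-9 does use it, and V1 PHQ-9 is already collected.

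At stake is some power in a trial of 76 randomized patients, and an unambiguous primary result.

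**Working it through.** **Step 1: the plan's own figure.** Inputs from the sample-size text: f = 0.30, alpha 0.05, power 0.80, r = 0.5, two groups. Two measurements (m = 2) are inferred from baseline and day 84.

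- Group factor: lambda = N f² m / (1 + (m − 1) r) = 68 × 0.09 × 2 / 1.5 = 8.16, on 1 and 66 df. Power is 0.804, so N = 68 reproduces. Dropout: 68 / 0.9 = 75.6, rounded up to 76, also reproduces.
- Interaction: lambda = N f² m / (1 − r) = 68 × 0.09 × 2 / 0.5 = 24.48. Power is 99.8%, and N = 24 would be enough.

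The size of 68 therefore comes from the group factor, whereas the analysis text gates on the interaction.

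**Step 2: what f = 0.30 means at day 84.** In a two-by-two layout an interaction of f corresponds to a difference in changes of 4f = 1.2 SD. Read as the group effect averaged over both visits, f = 0.30 is an average difference of 2f = 0.6 SD. With equal baselines after randomization this is again 1.2 SD at day 84. This is a detectability limit, since the protocol states no expected difference.

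**Step 3: relative variance.** Assume SD 1 at both visits and correlation r.

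- Change score, which is the two-visit interaction with free baseline means: 2(1 − r).
- Day-84 score adjusted for V1: 1 − r².
- Ratio of adjusted to change: (1 + r)/2.
- At r = 0.5: 1.00 against 0.75, ratio 0.75.

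**Step 4: power at 34 per arm, two-sided 0.05.** The standard error is √(2 × variance / 34), with noncentral t on 66 df (change) or 65 df (adjusted). Example at an assumed 0.6 SD and r = 0.5:

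- Change: SE = √(2 × 1.00 / 34) = 0.243; 0.6 / 0.243 = 2.47; power 68%.
- Adjusted: SE = √(2 × 0.75 / 34) = 0.210; 0.6 / 0.210 = 2.86; power 80%.

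| Assumed day-84 difference | r | Change score | Baseline-adjusted |
|---|---|---|---|
| 0.5 SD | 0.5 | 53% | 65% |
| 0.6 SD | 0.5 | 68% | 80% |
| 0.69 SD | 0.5 | 80% | 90% |
| 0.8 SD | 0.5 | 90% | 96% |
| 1.2 SD | 0.5 | 99.8% | about 100% |
| 0.6 SD | 0.7 | 88% | 93% |

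**Step 5: if more than the two-visit interaction is required.** These figures come from simulation at 0.6 SD and r = 0.5 with compound symmetry and Bonferroni correction. The comparator is the adjusted contrast at 80%.

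- Two-visit gate plus a corrected day-84 group comparison: 47% with 2 comparisons, 40% with 4, about 36% with 6.
- Four-visit gate alone: 57% to 71%, depending on whether the effect wanes, is sustained or is transient. It falls clearly below the two-visit 68% only in the waning case.
- Four-visit gate plus a corrected day-84 comparison: about 30% to 50%.

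The protocol specifies neither the four-visit gate nor the second criterion, and it does not rule them out.

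**Step 6: effect of selecting on V1.** Normal scores with r = 0.5 (an assumption) were truncated at V1 alone, or at V0 and V1, at 0 or 0.5 SD. The observed correlation fell to 0.26–0.33. The V1 variance shrank too, and the ratio of adjusted to change variance rose from 0.75 to 0.84–0.92. Under such selection adjustment saves about 8% to 16% of the variance, not 25%.

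**The case against.** The strongest defence is that the interaction is itself the primary test. If only V1 and V2 enter the model, group-by-time is a single 1-df test of exactly the stated endpoint at 0.05. Post-hoc comparisons come after it and take no power from it. It is unbiased under randomization and holds alpha. **This stands.** On that reading the cost is only the gap between the two power columns above. The text, however, does not say that this is the reading.

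Second, model details are commonly left to the SAP, and baseline as a response is inferred from the sample-size text. A mixed model with baseline means constrained equal would fit the analysis paragraph and recover nearly all the loss. **This stands in part.** The gate and the correction are stated in the protocol itself, so they are not simply details left for later.

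Two stronger readings are tempting, and the documents support neither.

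- *The plan costs 10 to 40 points of power.* That range needs an assumed difference of about 0.6 to 0.7 SD, and its upper part needs a corrected day-84 comparison as a further condition of success or V3 and V4 in the gate. The protocol gives no expected difference and states neither condition. At 1.2 SD and r = 0.5, even the gate with corrected comparisons loses only about 0 to 2 points.
- *Enrolling only patients with persisting symptoms lowers r and so makes change scores worse still.* Selection does lower r, but it also shrinks the V1 variance, and the second effect dominates. Step 6 shows the advantage of adjustment getting smaller. Putting r = 0.3 into (1 + r)/2 would wrongly suggest a 35% saving, because that formula assumes equal variances at both visits.

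**Conclusion.** The point holds as a moderate improvement. For one two-arm contrast at one visit, the gate and the correction are unnecessary, and they leave the decisive test unclear. Under the two-visit reading with free baseline means, the planned test is valid but less efficient than a baseline-adjusted one.

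At 34 per arm, r = 0.5 and equal variances, the gain is about 12 points of power at 0.5 or 0.6 SD, 10 at 0.69 SD, 6 at 0.8 SD and negligible at 1.2 SD. At r = 0.7 and 0.6 SD it is about 4–5 points. It is smaller than the formula implies if selection on V1 narrows the baseline variance. All these differences are assumptions of this review.

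A reader might infer an error that invalidates the result and must be corrected before the trial can be interpreted. The documents do not support that: the type I error is kept and the estimate is unbiased.

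**What to change.** Replace the gate sentence for the primary endpoint, in the protocol or in the SAP before unblinding, with wording such as:

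> The primary test is the BA-minus-mindfulness difference in PHQ-9 at day 84, estimated from a linear mixed model with V1 PHQ-9 as covariate (or with baseline means constrained equal), visit, treatment and treatment-by-visit. It is tested once at two-sided alpha 0.05, whatever the overall interaction shows. The contrasts at days 180 and 365 from the same model are secondary.

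The cost is wording only. V1 PHQ-9 is already collected, and no visit, assessment or sample-size change is needed.

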#### Secondary outcomes

Change in Patient Health Questionnaire-9 (PHQ-9) score from Baseline (V1) to days 84, 180 (V2, V3) and 365 (V4).Change in EuroQol- 5 Dimension (EQ-5D) score from Screening (V0) to days 84, 180 and 365 days (V2-V4).Change in modified Rankin Scale (mRS) from Screening (V0) to days 84, 180 and 365 (V2-V5).Return to work from Screening (V0) to days 84, 180 and 365 days (V2-V4).Incidence of major cardiovascular events defined as nonfatal stroke (ischemic or hemorrhagic), nonfatal myocardial infarction (including acute coronary syndrome requiring emergency vascularisation), and vascular death (i.e. sudden cardiac death and death from acute myocardial infarction, ischemic or hemorrhagic stroke, heart failure, cardiovascular procedures, pulmonary embolism, or peripheral artery disease) within one year of the index event.Recurrent ischemic or hemorrhagic stroke or TIA (transient ischemic attack; defined as transient neurological deficit < 24 h and absence of DWI (Diffusion-weighted imaging) positive lesions on MRI (Magnetic resonance imaging)) within one year of the index-event.All-cause mortality at 14 months.

Regular mortality follow-ups will be done for gathering information on deaths in the study sample. Death-certificates will be provided by local health authorities, causes of death will be specified using the International Classification of Diseases (ICD)-11.

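### Kolmogorov-Smirnov and Levene pre-tests on the trial data choose the model and scale for continuous secondary endpoints, while the primary endpoint has an unconditional mixed model

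*Protocol article*

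**What the plan says.** The analysis paragraph after Table 1 (Methods, Study description and study design) sets two rules.

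- Primary endpoint, with no condition attached: "For the primary endpoint, a linear mixed model will be performed".
- Secondary endpoints, conditionally: "Continuous secondary endpoints will be analysed using linear mixed models and subsequent post-hoc tests if the requirements for this strategy are met". The requirements are "tested by Kolmogorov-Smirnov tests and Levene’s tests". On failure, "In cases where the assumptions of normality or variance homogeneity are violated, a monotonic transformation of variables will be performed". After that, "If this first step is not successful, corresponding non-parametric tests will be used".

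The paragraph does not name the transformation, the criterion for its success, the replacement test, the variant of the Kolmogorov-Smirnov test, or the quantity tested (raw scores, changes or residuals).

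The Secondary outcomes section lists EQ-5D change at days 84, 180 and 365, mRS change ("Change in modified Rankin Scale (mRS) from Screening (V0" and onward), and this item: "Change in Patient Health Questionnaire-9 (PHQ-9) score from Baseline (V1) to days 84, 180 (V2, V3) and 365 (V4". Its day-84 component is also the sole entry under Primary outcomes.

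On populations, the paragraph says: "All primary analyses will be performed on the ITT population". It does not say the same of the secondary analyses.

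**The concern.** A rule that picks the analysis from the outcome data leaves open what will be estimated. Depending on the tests, the same endpoint may be reported as a difference in points, as a difference on a transformed scale, or as a rank comparison without an effect size in points. The scale could differ between endpoints and between visits of one endpoint.

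The two rules also collide. The day-84 PHQ-9 change is analysed unconditionally as primary and conditionally as secondary. Days 180 and 365, which carry the trial's long-term question, fall only under the conditional rule.

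At stake is whether the secondary results can be read, compared with each other and compared with the primary result. There is a further possible loss. A standard single-visit rank test would leave out patients who miss that visit, although a mixed model would use their other visits.

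**Working it through.** **1. Sample size for the check.** The plan needs 68 evaluable patients (34 per group) from f = 0.30, r = 0.5, two measurements, α = 0.05 and power 0.80. For the between-group factor, λ = f²·N·m / (1 + (m − 1)·r) = 0.09 × 68 × 2 / 1.5 = 8.16 with 1 and 66 degrees of freedom. This gives power 0.804, so 68 reproduces. With 10% dropout, 68 / 0.9 = 75.6, so 76, which also reproduces.

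**2. How often the first check fails.** The document gives no distributions, so these are assumptions: PHQ-9-like, gamma with mean 8 and SD 5, rounded; EQ-5D-like, 1 minus gamma(1.2, 0.25), capped at 1; mRS-like, levels 0 to 4 with probabilities .10, .25, .30, .25, .10. Each simulated sample of n = 68 was tested at 0.05, once with the plain Kolmogorov-Smirnov test (mean and SD estimated from the sample) and once with its Lilliefors correction. The PHQ-9-like and EQ-5D-like data were retested after a square root (reflected for EQ-5D).

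| Data | Fails first check: plain / Lilliefors | Still fails after square root: plain / Lilliefors |
|---|---|---|
| PHQ-9-like | 27% / 88% | 1% / 33% |
| EQ-5D-like | 49% / 96% | 0% / 18% |
| mRS-like | 95% / 100% | – |

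**3. Where a sample ends up.** If the samples that fail after transformation are taken as a subset of those that failed before, subtraction gives the approximate shares:

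| Data, test variant | Original scale | Transformed scale | Rank test |
|---|---|---|---|
| PHQ-9-like, plain | 100 − 27 = 73% | 27 − 1 = 26% | 1% |
| PHQ-9-like, Lilliefors | 100 − 88 = 12% | 88 − 33 = 55% | 33% |
| EQ-5D-like, plain | 100 − 49 = 51% | 49 − 0 = 49% | 0% |
| EQ-5D-like, Lilliefors | 100 − 96 = 4% | 96 − 18 = 78% | 18% |

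Once the first check fails, the transformed scale is the most common end point in every row. Whether it fails depends heavily on the test variant, which the plan leaves open.

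**4. Testing each arm and adding Levene.** With 34 per arm, a Kolmogorov-Smirnov test in each arm and one Levene test make three tests per endpoint and visit. If they were independent at 5%, even perfectly normal data would fail with probability 1 − 0.95³ = 0.143. Simulated failure rates, plain / Lilliefors, were: normal data 5% / 13%; skewed PHQ-9 14% / 80%; EQ-5D-like 9 to 10% / 65 to 67%; a seven-level mRS 30% / 99.7%. The shapes differ somewhat from step 2, but the pattern is the same.

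**5. Error rate and bias at day 365.** Assumptions: 38 per arm, PHQ-9 SD 5.5, correlation 0.5, about 20% or more missing, transformation step skipped. The retained model was approximated by regressing day 365 on group and an earlier visit, with estimate b_group + b_earlier × (difference in earlier means over all patients). The data-driven strategy switched to a complete-case Mann-Whitney test when a pre-test failed (Lilliefors in each arm, or Levene).

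| No true effect | Retained model, type I error | Data-driven switch, type I error | Complete-case mean difference |
|---|---|---|---|
| Random dropout, normal | 0.056 | 0.054 | 0.05 |
| Random dropout, skewed | 0.053 | 0.047 | 0.03 |
| Informative dropout, normal | 0.055 | 0.066 | −1.34 |
| Informative dropout, skewed | 0.044 | 0.111 | −1.20 |

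Informative here means that dropout depended on the earlier score in opposite directions in the two arms. The retained model's mean estimate was about 0 in every row.

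**The case against.** The strongest reply is that the cascade is prespecified, concerns only secondary endpoints of a proof-of-concept trial, and is run by a statistician blinded to group. An SAP is announced, and details such as the test variant, the transformation and the named rank test commonly belong there. That is fair as to the details, and their absence is not the point. The conditional rule itself stands in the protocol, and filling in its steps would still leave the data to choose the scale.

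Several stronger readings are tempting, but the document does not support them:

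- *PHQ-9 and EQ-5D will mostly end in rank tests.* This skips the transformation step. Under the assumptions above, most samples that fail the first check are rescued by a square root. Only mRS-like data fail almost always with either test variant at n = 68.
- *mRS is certainly caught.* The rule covers continuous endpoints, and mRS is not expressly called continuous. It is caught only if its change score is treated that way.
- *Covariate adjustment and the ITT estimate are lost.* No covariates are named for these models, and ITT is stated only for primary analyses.
- *Results will be complete-case.* The replacement tests are unnamed, and rank methods for repeated measures are not excluded. The loss is possible, not certain.
- *The pre-test inflates false positives.* It did not under completely random dropout. The inflation in step 5 comes from complete-case handling under an assumed informative dropout.

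Two further objections stand in part. First, the outcomes are changes, and a mixed model's assumptions concern residuals, so raw-score failure rates are only indicative. Under other assumptions at n = 68, Lilliefors failure was 21% for a roughly symmetric PHQ-9 change, 74% for a PHQ-9 change from a baseline of at least 10, 56% for EQ-5D change, and 46% for baseline-adjusted mRS residuals. The rates move a good deal with the assumptions. Second, with skewed data and random dropout the switch had more power for a 3.3-point effect (0.722 against 0.637), so a rank analysis has some value as a supplement.

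**Conclusion.** The concern holds in a limited form. The protocol lets pre-tests on the trial data decide whether a continuous secondary endpoint is analysed on its own scale, on a transformed scale or by a non-parametric test, and it applies a different, unconditional rule to the same day-84 PHQ-9 change as primary endpoint. At n = 68, under the assumed shapes, the original scale would be abandoned in about 27% to 88% of PHQ-9-like and 49% to 96% of EQ-5D-like samples, the lower figure with the plain test and the higher with Lilliefors. The usual consequence of failure is an estimate without a direct reading in points; a rank test is the less common one (about 1% to 33% and 0% to 18%). A bias of about 1.2 to 1.3 PHQ-9 points arises only if the rank test is a complete-case one and dropout is informative as assumed.

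All these rates rest on distributions that the document does not give. That the data choose the scale rests on the text alone. The primary analysis is not affected. This is a change the plan should make, not a threat to the trial's main conclusion.

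**What to change.** Delete the pre-test cascade and state instead:

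- PHQ-9 and EQ-5D at days 84, 180 and 365 are analysed with the same linear mixed model as the primary endpoint, on the original scale, whatever any normality or variance test shows. Robust or bootstrap confidence intervals are used if residuals look non-normal.
- mRS is analysed with an ordinal method, such as a proportional-odds model. Other valid ordinal choices exist; what matters is that one is fixed.
- Transformed-scale and rank analyses are sensitivity analyses only.

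This also puts the day-84 PHQ-9 change under one rule. The change should be made and dated before unblinding. It costs a revision of the analysis wording and slightly more programming. The planned 68 evaluable and 76 randomised patients, the visits and the data collected stay as they are.

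### The likelihood-ratio tests named for AEs and SAEs exceed the nominal 5% error at 38 per arm when event rates are roughly 3% to 12%

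*Protocol article*

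**What the plan says.** All analysis statements are in the protocol article, Methods, Study description and study design, in the statistical text after Table 1.

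- Safety data: side-effects, "adverse events (AE) and severe adverse events (SAE) will be analysed with descriptive statistics and likelihood-ratio tests".
- Level: "All analyses will be performed at a significance level of α = 0.05".
- Population: "The safety population includes all patients as randomized".
- Size: "Assuming a drop-out rate of 10% during the intervention period, 76 patients are planned to be randomized", and "The allocation ratio is 1:1".
- A further sentence, placed between the one on comparing demographic data and the one on presenting baseline characteristics: "Dichotomous variables will be analysed with likelihood-ratio tests".

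For continuous secondary endpoints the same text gives an assumption check, a transformation step and a non-parametric fallback. For binary data it gives no check and no fallback. No event rate is stated. Under Arms and interventions, somatic side effects are described as unlikely.

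**The concern.** The likelihood-ratio statistic for a 2x2 table follows a chi-square distribution only approximately, and the approximation needs reasonable expected counts. With 38 patients per arm and an event risk of 5%, the expected count is 38 x 0.05 = 1.9 per arm. At such counts the statistic tends to be too large, particularly when one cell is zero, so the p-value is too small.

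What is at stake is a false safety signal. Two or three chance events more in one arm could be reported as a significant difference in SAEs, either against the behavioural activation arm or in its favour.

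**Working it through.** **The plan's own figures.** The article asks for a "total necessary sample size of 68 (34 participants per group) at V2". With the repeated-measures between-group formula, lambda = f² x N x m / (1 + (m − 1)r) = 0.09 x 68 x 2 / 1.5 = 8.16, on 1 and 66 degrees of freedom. Power is 0.804 at N = 68 and 0.792 at N = 66, so 68 is reproduced. Inflating for dropout, 68 / 0.90 = 75.6, rounded up to 76, which is 38 per arm. The safety population is everyone randomised, so 38 per arm applies; 34 per arm is a sensitivity case.

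**The statistic.** G = 2 x Σ O ln(O/E), referred to chi-square with 1 degree of freedom (critical value 3.841). For 0/38 versus 3/38 the expected counts are 1.5 events and 36.5 non-events in each arm:

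G = 2 x [3 ln(3/1.5) + 35 ln(35/36.5) + 38 ln(38/36.5)] = 4.159 − 2.937 + 3.061 = 4.28, so p = 0.0385.

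**Comparison with other tests, 38 per arm (two-sided p).**

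| Split | Likelihood ratio | Pearson | Boschloo | Fisher |
|---|---|---|---|---|
| 0 vs 3 | 0.039 | 0.077 | 0.167 | 0.240 |
| 0 vs 4 | 0.016 | 0.040 | 0.085 | 0.115 |

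The Boschloo values condition on the two arm sizes and maximise over the common event rate. Direct enumeration ordered by the two-sided Fisher p-value gives the same results.

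**A check by counting.** If three events occur in 76 patients and there is no true difference, the chance that all fall in one arm is 2 x C(38,3) / C(76,3) = 2 x 8436 / 70300 = 24.0%. The likelihood-ratio test declares every such split significant.

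**True type I error.** Size(p) = Σ over a, b of Bin(a; 38, p) x Bin(b; 38, p), summed over the tables with G > 3.841. The event rate p, common to both arms, is an assumed range because the article gives none.

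| Event rate | Likelihood ratio | Pearson | Fisher |
|---|---|---|---|
| 1% | 0.9% | 0.1% | 0.0% |
| 2% | 3.7% | 0.6% | 0.0% |
| 3% | 6.7% | 1.7% | 0.1% |
| 5% | 9.1% | 4.1% | 0.3% |
| 8% | 7.7% | 5.7% | 1.1% |
| 10% | 6.6% | 5.8% | 1.5% |
| 15% | 5.4% | 5.3% | 2.4% |
| 20% | 5.0% | 5.0% | 2.7% |
| 30% | 5.2% | 5.2% | 3.0% |

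With 34 per arm the likelihood-ratio size peaks at 9.0% near a 6% rate. At a 5% rate Pearson's test on the same tables stays at 4.1%, so the excess there comes from the chosen statistic and not from small samples alone.

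**The case against.** Several counter-arguments have weight.

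- **Scope.** A reader might infer that cardiovascular events, recurrent stroke and "All-cause mortality at 14 months" are also to be tested this way and so carry the same inflated error. The text does not establish that. The sentence on dichotomous variables sits between two statements about demographic and baseline data, and it pairs with analysis of variance for continuous variables, although continuous secondary endpoints already have linear mixed models. Baseline comparison is the more natural reading. The list of secondary outcomes names no test. Only side-effects, AEs and SAEs are clearly covered.
- **Generality.** A reader might also infer that the test over-rejects for every sparse outcome. It does not: at rates of 2% or below its size is under 5%, because three or more events seldom occur, and from about 15% the excess is negligible. The band is about 3% to 12%, and whether the trial falls in it is an assumption.
- **Comparator.** Part of the gap between 0.039 and Fisher's 0.24 is Fisher's own conservatism. Pearson is the fairer contrast. It does not reject 0 versus 3, but it does reject 0 versus 4 (p = 0.040).
- **Unseen analysis plan.** The article says one will be developed, and it could specify an exact reference distribution. That limits the point but does not remove it, because the article itself names the test and the level.
- **Consequence.** The trial is a proof of concept, AEs are also described descriptively, and no stated decision depends on an AE p-value. This stands, and it is why the point is minor.

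**Conclusion.** The point holds for side-effects, AEs and SAEs. As stated, and with the usual chi-square reference, the test has a true error of up to 9.1% against a nominal 5% at 38 per arm, and it calls 3 events versus 0 significant. This rests on two assumptions: the chi-square reference, and an event rate within about 3% to 12%. Outside that band there is no material inflation.

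The same would apply to binary clinical outcomes only if the dichotomous-variables sentence is meant to cover them. The documents do not support a claim that the cardiovascular and mortality results will be wrong. A false safety signal is possible rather than expected. The PHQ-9 primary analysis is untouched. Severity: minor.

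**What to change.** For side-effects, AEs, SAEs and any other sparse binary comparison, replace the likelihood-ratio chi-square with an exact test (for example Boschloo or Fisher), report the risk difference with an exact 95% confidence interval, and keep AE reporting mainly descriptive. State also whether the sentence on dichotomous variables refers to baseline data only or includes the binary secondary outcomes.

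With Boschloo or Fisher, neither 0 versus 3 nor 0 versus 4 is significant. With Fisher, the first significant split against zero is 6 (p = 0.025; 5 versus 0 gives 0.054), and its size is at most 3.0% across assumed rates of 1% to 30%.

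The cost is one sentence, best added before unblinding, using standard software and with no change to sample size or data collection. P-values will be somewhat larger and power lower on comparisons for which the trial was not sized.
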